# The effect of nebulized salbutamol or isotonic saline on exercise-induced bronchoconstriction in elite skaters following a 1,500-meter race: study protocol for a randomized controlled trial

**DOI:** 10.1186/1745-6215-14-204

**Published:** 2013-07-09

**Keywords:** Elite athletes, Exercise-induced bronchoconstriction, Salbutamol, Forced oscillation technique, Small airways

## Abstract

**Background:**

Prevalence of exercise-induced bronchoconstriction (EIB) is high in elite athletes, especially after many years training in cold and dry air conditions. The primary treatment of EIB is inhaling a short-acting beta-2-agonist such as salbutamol. However, professional speed skaters also inhale nebulized isotonic saline or tap water before and after a race or intense training. The use of nebulized isotonic saline or tap water to prevent EIB has not been studied before, raising questions about safety and efficacy. The aim of this study is to analyze the acute effect of nebulized isotonic saline or salbutamol on EIB in elite speed skaters following a1,500-meter race.

**Methods:**

This randomized controlled trial compares single dose treatment of 1 mg nebulized salbutamol in 4 mL of isotonic saline, or with 5 mL of isotonic saline. A minimum of 13 participants will be allocated in each treatment group. Participants should be between 18 and 35 years of age and able to skate 1,500 m in less than 2 min 10 s (women) or 2 min 05 s (men). Repeated measurements of spirometry, forced oscillation technique, and electromyography will be performed before and after an official 1,500-m race. Primary outcome of the study is the difference in fall in FEV_1_ after exercise in the different treatment groups. The trial is currently enrolling participants.

**Discussion:**

Elite athletes run the risk of pulmonary inflammation and remodeling as a consequence of their frequent exercise, and thus increased ventilation in cold and dry environments. Although inhalation of nebulized isotonic saline is commonplace, no study has ever investigated the safety or efficacy of this treatment.

**Trial registration:**

This trial protocol was registered with the Dutch trial registration for clinical trials under number NTR3550

## Background

Exercise-induced bronchoconstriction (EIB) is the most common chronic condition in elite athletes [1]. Especially endurance athletes who reach high ventilation in cold, dry air on a regular basis are susceptible to EIB [1,2]. A study using a canine model highlighted the negative effect of dry air on the airways as it leads to airway inflammation and airway remodeling [3]. In humans this find has been confirmed in bronchial biopsies from competitive elite skiers, showing signs of eosinophilic and neutrophilic airway inflammation in the lungs, similar to those seen in asthma [4].

In elite speed skaters intense training may cause thoracic pain and cause EIB [5]. For this reason many speed skaters use a roll-collar in training to warm and humidify inhaled air. Beuther *et al.* already showed that warming the inhaled air can reduce EIB [6]. In competition, due to aerodynamics, this method cannot be used. In an effort to reduce EIB and thoracic pain, international professional speed skaters nowadays inhale nebulized isotonic saline or tap water before and after a race or intense training session. In EIB, the primary treatment is a short-acting beta-2-agonist such as salbutamol [1,7]. This treatment reduced smooth muscle contraction very effectively, but still is an example of symptomatic therapy. The recommended dosage of nebulized salbutamol is 5 mg, which would require a therapeutic use exemption for participating athletes from the world anti-doping agency (WADA) (http://www.wada-ama.org). Although such a dosage is safe in highly trained athletes [8], we routinely recommend using 1 mg of salbutamol, which we believe leads to substantial reductions in EIB in this population. The use of nebulized isotonic saline treat EIB has not been studied before, raising questions about safety and efficacy.

Spirometry before and after exercise is the golden standard for assessing the occurrence and severity of EIB [7]. A fall in forced expiratory volume in 1 s (FEV_1_) >10%, after exercise (>95% predicted heart frequency) indicates EIB. A potential disadvantage of spirometry is the use of a forced maneuver and not everybody is able to perform reliable measurements. In addition the maneuver requires a forced deep inspiration which in asthmatic children with EIB may lead to bronchodilation [9], and an underestimation of EIB. The forced oscillation technique (FOT) may be used to evaluate the patency of the airways without the need of forced breathing [10]. Another substitute for evaluating lung function without the need of forced breathing may be electromyography (EMG), however, it has not been used to evaluate EIB [11,12].

The aim of the study is to analyze the effect of nebulized isotonic saline or salbutamol on EIB in elite speed skaters following a 1,500-m race using spirometry, FOT, and EMG.

## Methods

### Design

This study is a prospective, randomized, double-blind, placebo, treatment, and non-intervention controlled study, consisting of three parallel groups. Participants will be randomized to receive either no intervention (control), 1 mg of nebulized salbutamol (treatment), or nebulized isotonic saline (placebo). An overview of the timing of randomization and data collection can be seen in Figure 1.

**Figure 1 F1:**
[figure not shown]
**Timing if randomization and data collection of the study.** EMG, Electromyography; FOT, Forced oscillation technique; VAS, Visual analogue scale.

This trial protocol was ethically approved by the Regional Ethical Committee (RTPO), Leeuwarden (primary) and the Central Committee on Research Involving Human Subjects (CCMO), The Hague (secondary) and was registered with the Dutch trial registration for clinical trials (http://www.trialregister.nl) under number NTR 3550. All participants signed a written informed consent form.

### Setting and participants

Participants are recruited from the provincial selection teams and professional skating teams in the Netherlands. All skaters in these teams will be invited to participate in the study after they will be screened for eligibility.

### Inclusion criteria

Skaters should be between 18 and 35 years of age and be able to skate the 1,500 m in less than 2 min 10 s (women) and 2 min 05 s (men), and be able to perform lung function tests according to current standards [13].

### Exclusion criteria

Skaters will be excluded if they had: a respiratory infection within 6 weeks prior to the tests for which medication has been prescribed; an FEV_1_ <70% of predicted; ultrasonic nebulization with tap water or saline solutions within 48 h before testing; use of short-acting beta agonists 8 h before exercise; use of long-acting beta agonists 24 h before exercise; use of a leukotriene-receptor-antagonist 36 h before exercise.

**Figure 2 F2:**
[figure not shown]
A flow diagram of the progress through the phases of the study.

### Pulmonary function measurements

FOT measurements will be performed with R.O.S., Oscilink®, Sensormedics® to measure general respiratory resistance and reactance. FOT measurements will consist of three repeated measurements with nose clipped and with hands supporting cheeks and base of the mouth [10]. FOT measurements will be performed before and at 10, 15, and 30 min after exercise. The average of resistance and reactance values will be used for statistical analysis.

A Masterscope® Jaeger®, will be used to measure flow-volume loops in accordance with current ERS/ATS guidelines [13]. Lung function will be calculated from the best curve. Flow volumes will be measured in duplicate before and at 11, 16, and 31 min after exercise, the best values at each time point retained for analysis. Feeling of dyspnea and thoracic pain will be evaluated using a visual analogue scale (VAS) after every complete spirometry measurement.

EMG of the diaphragm and intercostal muscles will be derived transcutaneously from pairs of single electrodes (disposable Neotrode, ConMed Corporation, NY) [11]. To obtain the electrical activity of the diaphragm, two electrodes will be placed bilaterally below the costal margin in the nipple line (frontal lead of diaphragm) and two bilaterally on the back at the same level (dorsal lead of diaphragm). The mean value of the processed data of the frontal and dorsal leads of the diaphragm represented the electrical activity of the whole diaphragm. A common electrode will be placed at the height of the sternum.

### Exercise provocation challenge

Exercise testing for measuring EIB will be performed by skating 1,500 m. Cold, dry air will be obtained while testing in the local skating ring, IJsbaan Thialf, Heerenveen (http://www.thialf.nl).

### Outcomes

The primary outcome of the study is the difference in percentage fall in FEV_1_ from baseline after exercise in the different treatment groups. Secondary outcomes of the study are the difference in airway resistance and reactance in kPa/l/s at low frequency as measured with the FOT and difference in diaphragm and intercostal muscle activity in the logarithm of mean bottom ratio of respiratory muscle activity between the different treatment groups.

### Sample size

Numbers of study participants were calculated using the calculations of Dupont, and setting power of the study at 80% and *P*=0.05 [16]. Data used to produce these numbers came from research performed by Driessen *et al.*[17]. We expect no difference between placebo and control groups. Analyzing the protective effect of salbutamol in a randomized control trial, with an expected difference in FEV_1_ of 10% and a standard deviation from the mean of 6% the number of participants was set at 13 per group. Therefore the total number of randomized participants will be at least 39. In the aforementioned research performed by Driessen *et al.*, 95% of patients completed the study. Therefore the enrolled patient count will be 1.05 times the total number (39•1.05=41).

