### Data analysis

Best values of spirometric measurements, mean values of FOT measurements and EMG measurements recordings of 60 s during FOT measurements will be used for statistical calculations. Data will consist of a set of comparing participants who nebulized 1 mg Salbutamol, isotonic saline, and one set of controls. Once gathered, data will be analyzed with SPSS analytical software after testing for normality with a Shapiro-Wilk test. Difference between groups will be analyzed with a chi-square test for dichotomous variables and a one-way ANOVA, followed by a post-hoc Tukey’s test for continuous variables.

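### The stated 13 per group and 80% power do not follow from the stated 10% difference and 6% SD, so an input is misreported or a step is unstated

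*Protocol article*

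**What the plan says.** All figures are in the protocol article, under Methods.

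- **Sample size**, error rates: "setting power of the study at 80% and *P*=0.05".
- **Sample size**, effect, given in percent: "with an expected difference in FEV_1_ of 10".
- **Sample size**, spread and result: "a standard deviation from the mean of 6% the number of participants was set at 13 per group". The section multiplies this to at least 39 randomized, then adds 5% for drop-out to reach 41 enrolled. It also expects placebo and control not to differ.
- **Design**: the trial is described as "consisting of three parallel groups".
- **Outcomes**: the primary outcome is the percentage fall in FEV1 from baseline, compared between groups.
- **Data analysis**: "Difference between groups will be analyzed with a chi-square test for dichotomous variables and a one-way ANOVA", with Tukey's test as the post-hoc procedure for continuous variables.

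The Sample size section does not say whether the test is one- or two-sided, or whether the 6% is the SD of the percentage fall or of some other FEV1 quantity. It mentions no multiplicity adjustment, safety margin or allowance for skaters who do not respond to exercise.

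**The concern.** The section gives everything needed to recompute the group size: power, significance level, difference and SD. A standardized difference of 10/6 = 1.67 is very large, and 13 per group is far more than 80% power would require for it. The result therefore does not match its own inputs.

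What is at stake is how the result will be read. If SD 6% is right, the trial can detect differences well below 10 points, and a null result would be fairly informative. If the calculation really used a larger SD, 13 per group has little or nothing to spare, and the planned Tukey comparison would have less than the stated power. The published figures do not let a reader tell these cases apart.

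**Working it through.** **Inputs** (Sample size section): difference d = 10, SD s = 6, alpha = 0.05, power 80%, stated n = 13 per group. Assumption: two-sided test.

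**1. Attempt to reproduce 13.** Normal approximation: n = 2(1.960 + 0.842)² s²/d² = 2 × 7.85 × 36/100 = 5.65, so 6 per group. Exact two-sample t-test, with noncentrality (d/s)√(n/2) on 2n − 2 degrees of freedom:

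| n per group | Noncentrality | Power |
|---|---|---|
| 6 | 2.89 | 74.0% |
| 7 | 3.12 | 81.6% |
| 13 | 4.25 | 98.3% |

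The exact solution is n = 6.76, so 7 per group. The stated 13 is not reproduced; it is 13/7 = 1.86 times the required number.

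**2. Planned analysis.** One pairwise comparison under Tukey with three groups, using the pooled variance on 3n − 3 degrees of freedom and the studentized-range critical value divided by √2: power is 78.4% at n = 8, 84.2% at n = 9 and 96.0% at n = 13. Tukey therefore needs 9.

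**3. Other readings of the same inputs**, per group:

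| Reading | n |
|---|---|
| One-sided t-test | 6 |
| Paired | 6 |
| Wilcoxon inflation of the t-test | 8 |
| Three-group ANOVA F test, means 0, 0, 10 | 7 |
| Bonferroni, two comparisons | 9 |
| Bonferroni, three comparisons | 10 |
| Tukey, both salbutamol comparisons significant | 10 |
| Bonferroni for three, both salbutamol comparisons significant | 11 |

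None gives 13. The most demanding rests on conditions that the document does not state, and totals 3 × 11 = 33, against 39. Drop-out cannot explain the gap, because it is added after the 13.

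**4. What 13 per group detects if SD = 6.** Difference with 80% power: 6.9 points for one two-group t-test, 7.8 points for one pair under Tukey.

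**5. What SD would make 13 the answer.** With d = 10 and 80% power by the t-test, the exact requirement is n = 12 at SD 8.36 and n = 13 at SD 8.73. An SD between these rounds up to 13, so the SD would have to be about 8.4 to 8.7. One value in that range is 6 × √2 = 8.49, which gives n = 12.34, rounded up to 13. No such SD appears in the document. If it were 8.5, the noncentrality at n = 13 would be (10/8.5) × √6.5 = 3.00, and Tukey power for 10 points about 71%.

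**The case against.** The strongest defence is that the discrepancy is on the safe side. Taken at face value, the inputs give more than the stated 80% power at 13 per group, even under Tukey, and the protocol presents 39 as a minimum. That stands: on the stated figures nobody is under-recruited. It does not make the 80% correct, and the section presents 13 as the result of the calculation, not as a deliberate surplus.

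A second defence is that the figures may be reconcilable. The text does not say that 6% is the SD of the percentage fall. If it were the SD of a single FEV1 value and the two values were treated as independent, the SD of a change would be 6√2 and 13 would follow. This is possible but is inference. It supports saying that a step may be unstated, and it is why calling the figures impossible would go too far.

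A reader might also infer that the trial is underpowered, because Tukey power would be about 71% at SD 8.5. The documents do not support that. The 8.5 is an assumption obtained by working backwards from 13, and the method and earlier data that the section cites are not available here.

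The Discussion acknowledges that skaters without a substantial fall limit power. The Sample size section makes no allowance for this, so it does not account for the 13.

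**Conclusion.** The concern holds as a reporting inconsistency. The stated difference, SD, significance level and power require 7 per group (t-test) or 9 (one Tukey pair), not 13; at 13 the power is about 98% or 96%, not 80%. The exact counts assume a two-sided test and that 6% is the SD of the outcome being compared; a one-sided test moves the answer further from 13. Which figure is misreported, or which step is missing, cannot be determined from the document. The sample-size statement for the primary outcome needs correcting, but the inconsistency alone is no reason to change the number recruited.

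**What to change.** Keep 13 per group. Go back to the source calculation, state the SD of the percentage fall in FEV1 that was actually used and whether the test was two-sided, and restate power for the planned Tukey comparisons.

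- If SD 6% is right: state that 13 per group gives about 96% power for a 10-point difference, and 80% power for about 7.8 points, under Tukey (6.9 points for a single two-group t-test).
- If a larger SD was used: correct the 6% and restate the power. At an SD of 8.5, for illustration only, Tukey power for 10 points would be about 71%.
- If a further step led to 13: describe it.

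The cost is a check of the original calculation and a few sentences in the Sample size section. Group size and the analysis are unchanged. If a larger SD is confirmed, the restated power may be less favourable than 80%.

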### Randomization

Participants are randomized using a pre-generated randomization list. For randomization a linear congruential algorithm of Park and Miller with Bays-Durham shuffling was employed, using block sizes of two, four, and eight participants. Stratified minimization will commence using the number of intensive training years (> or <5 years) and the current use of asthma medication. A flow diagram of the progress through the phases of the study can be seen in Figure 1.

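### Block sizes of two, four and eight cannot balance three equal arms, and the plan does not say whether the block list or the minimisation governs allocation

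*Protocol article*

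**What the plan says.** The Design section of the protocol article describes a trial "consisting of three parallel groups" and says that participants are randomised to no intervention, nebulised salbutamol or nebulised saline. No allocation ratio is given. Equal allocation follows from the Sample size section, where "the number of participants was set at 13 per group" and "the total number of randomized participants will be at least 39", and from the abstract: "A minimum of 13 participants will be allocated in each treatment group". Enrolment is then raised to 41 to allow for dropout.

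The Randomization section gives two devices in consecutive sentences:

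- A list: "Participants are randomized using a pre-generated randomization list", built "using block sizes of two, four, and eight participants".
- A minimisation: "Stratified minimization will commence using the number of intensive training years (> or <5 years) and the current use of asthma medication".

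Nothing in the article says how the two work together.

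**The concern.** A permuted block keeps arms balanced because each completed block holds the arms in the intended ratio. With three equal arms, the block size must be a multiple of three. The stated sizes suit a two-arm 1:1 list. Used for three arms, every block is uneven, and the blocking no longer secures the minimum of 13 per arm.

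The minimisation sentence adds a second difficulty. Minimisation chooses each assignment from the characteristics of those already in the trial, so its assignments cannot be read off a list written beforehand. A reader cannot tell which procedure produced the assignments, and the procedure cannot be reproduced from the description. Allocation cannot be repaired in the analysis, so the account of it has to be right.

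**Working it through.** **Inputs.** Three arms (Design); 13 per group and 39 in total (Sample size); block sizes 2, 4 and 8, and two binary factors for minimisation (Randomization).

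**The plan's own totals.** 3 × 13 = 39, and 39 × 1.05 = 40.95, rounded to 41. Both reproduce.

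**Divisibility.** 2 = 0 × 3 + 2; 4 = 1 × 3 + 1; 8 = 2 × 3 + 2. The remainders are 2, 1 and 2, never 0, so no permitted block is balanced over three equal arms. An unstated unequal ratio does not explain the sizes: 2:1:1 would fit blocks of four and eight but not two, and it contradicts 13 per group.

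**If the blocks govern.** Simulated lists, with block sizes drawn at random, each block filled as evenly as possible, leftover places given to randomly chosen arms, and the list cut at the total:

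| Scheme | Total 39: all arms 13 | Total 41: every arm at least 13 | Total 41: smallest arm below 13 |
|---|---|---|---|
| Blocks 2/4/8, one list | about 8% | about 40% | about 60–62% |
| Blocks 2/4/8, four equally likely strata (assumed) | about 6% | about 31% | about 69% |
| Blocks 3/6, one list | about 80% | 100% | 0% |
| Simple randomisation | about 2% | about 11% | about 89% |

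The stated blocks therefore restrain imbalance to some degree, but they do not secure 13. With blocks of 3 and 6 run separately in four strata, the smallest arm still falls below 13 in about 29 to 37% of runs at a total of 41. Correct block sizes protect the minimum only on a single list.

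**If minimisation governs.** Three arms, total 41, the two stated factors taken as independent and split 50/50 (assumption). The smallest arm falls below 13 in about 0.05% of runs if assignment is deterministic, about 4% if the favoured arm is chosen with probability 0.9, and about 14% with probability 0.8. The last figure depends on the scoring rule, and the rate is lower when overall arm totals are also counted. A fair summary is about 0 to 10%, slightly more under the loosest scheme. The article gives no assignment probability.

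**Effect on power.** Two-sample t test, two-sided 5%, difference 10:

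| Arm sizes | SD 6 (stated) | SD 6√2 = 8.49 (sensitivity only) |
|---|---|---|
| 13 v 13 | 98% | 82% |
| 11 v 15 | 98% | 81% |
| 10 v 14 | 97% | 78% |

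At the stated SD, 80% power would need only 6 per group (normal approximation: 2 × (1.96 + 0.84)² × 36/100 ≈ 5.6) or 7 (t test). That 13 does not follow from these inputs is a separate matter, and the present point does not rest on it.

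**The case against.** The strongest reply is that minimisation rescues the design. If it drives allocation, three arms of about 13 are largely protected whatever the block sizes, and the 62% describes a trial that was not run. This stands as far as it goes: the 62% applies to blocks alone. It does not rescue the text, because if minimisation governs, the block sizes have no function and their statement is wrong. A list made in advance might supply the random element of a minimisation, but it would then need no blocks, and the article does not say this.

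A second reply is that the harm is small. Uneven blocks filled at random still give unbiased comparisons, about two-thirds of the shortfalls are a smallest arm of exactly 12, and power barely moves. The totals are also minimums, so a shortfall of one could be met by enrolling further. All of this stands.

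A reader might infer more: that the sizes betray a two-arm list for salbutamol and saline, that controls were allocated outside it, and that every contrast with control is therefore non-randomised. The abstract, which sets out only the two nebulised treatments, makes this tempting. The documents do not support it. The Design section says that participants are randomised to control as well, no passage describes a separate route for controls, and a separate route could itself be random. Nor does the article claim balance within each race date; date is not among the stated factors.

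**Conclusion.** The point holds in a limited form. The stated block sizes cannot balance three equal arms; that is arithmetic and rests only on the 1:1:1 ratio implied by 13 per group and 39 in total. The block list and the minimisation are stated together without saying which governs, and they cannot both determine the assignments as described. The chance that an arm ends below 13 of 41 is about 62% on one blocked list, under the filling rule assumed above, and about 0 to 10% under minimisation for most assignment probabilities. The loss of power is negligible at the stated SD and a few percentage points at most at the larger one. The fault lies in whether the allocation can be carried out and reproduced, and in the promised minimum. It is not evidence of bias or of non-randomised controls.

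**What to change.** State one allocation method that covers salbutamol, saline and no intervention. Either would do:

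- a single 1:1:1 permuted-block list with block sizes that are multiples of three, for example 3 and 6 in random order; or
- three-arm minimisation on training years and asthma medication, with a stated random element and no fixed block list.

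The Trial status section places test dates in December 2012, February 2013 and the fall of 2013, and the article appeared in July 2013, so participants at the third date may still be unallocated. For them, minimisation that counts those already allocated is preferable. Restarting with blocks of 3 and 6 keeps the earlier imbalance: if 27 of 41 were already allocated on 2/4/8 blocks (an assumption, about two-thirds), the smallest arm would still fall below 13 in about 56% of single lists, against about 61% with no change.

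Report how participants at the earlier dates, including controls, were actually allocated, and correct the Randomization section to match. The cost is a rewritten paragraph and a new allocation routine for the remaining participants. The change of method needs no extra participants, though neither option guarantees 13 per arm if imbalance has already built up.

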### Blinding

The study medication will be delivered to the skating ring in a standard syringe, containing either 1 mg salbutamol in isotonic saline or solely isotonic saline with a standard label. The lack of inhalation in the control group cannot be masked. Assessment of lung function will be assessed without knowledge of the received treatment.

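### Allocation is described both as a blocked, pre-generated list and as stratified minimisation, so the method is not identifiable; the stated block sizes do not fit three arms, and exactly 5 training years has no level

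*Protocol article*

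**What the plan says.** The protocol article sets out allocation in one short paragraph, under Randomization. It contains two descriptions:

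- **A list.** "Participants are randomized using a pre-generated randomization list". The random number generator is named, and the list is built "using block sizes of two, four, and eight participants".
- **Minimisation.** "Stratified minimization will commence using the number of intensive training years (> or <5 years) and the current use of asthma medication".

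No sentence links the two. The Design section describes the trial as "consisting of three parallel groups" (no intervention, salbutamol, isotonic saline). Under Sample size, "the number of participants was set at 13 per group", giving at least 39 randomised and 41 enrolled.

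The Data analysis section compares groups on continuous variables by one-way ANOVA followed by Tukey's test. Neither allocation factor appears in that analysis.

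**The concern.** A pre-generated list fixes the order of arms before anyone is enrolled. Minimisation works out each arm at enrolment, from the factor levels of the new participant and of those already allocated. If the list decides, the two factors are not being balanced by minimisation. If minimisation decides, the list and its blocks are not the allocation. The paragraph does not say which applies, or when.

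Three things depend on the answer: whether the procedure can be reported and reproduced, whether the arms can be expected to be balanced on current asthma medication and training years, and which factors the analysis should carry. Factors used to restrict allocation normally belong in the primary model. The one-way ANOVA has no place for them, so it would not correct a chance imbalance and would not use the precision they may offer.

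**Working it through.** The protocol gives no figure for this point, so there is none to reproduce. The check sets the statements side by side and adds some small arithmetic.

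**1. Do the two descriptions give the same arm?**
Not in general. A simulation was run with 41 skaters (Sample size), three arms (Design) and two binary factors (Randomization). Two inputs are assumptions, because the document does not supply usable values: each factor is present in 50% of skaters, and the list uses blocks of 3, 6 or 9. For each skater it asked whether the next arm on the list was among those that minimisation (range criterion) would choose.
- Share of skaters for whom it was not: about 45%.
- 5th to 95th percentile over simulated trials: 32% to 61%.

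Other prevalences were not run. The result shows only that the two rules often part company in a trial of this size.

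**2. Does reading it as stratified blocks work?**
A block balanced 1:1:1 over three arms needs a size divisible by 3.

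| Stated block size | Remainder on division by 3 | Most even split possible |
|---|---|---|
| 2 | 2 | 1:1:0 |
| 4 | 1 | 2:1:1 |
| 8 | 2 | 3:3:2 |

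None of the three sizes can be balanced. Blocks of 3 (1:1:1) and 6 (2:2:2) can.

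**3. Do the factor levels cover everyone?**
Training years are split into more than 5 and less than 5. A skater with exactly 5 has no level under either allocation method.

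**4. What would adjustment cost?**
With 39 analysed, the one-way ANOVA has 39 − 3 = 36 residual degrees of freedom. Adding two binary factors leaves 39 − 3 − 2 = 34.

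**The case against.** The strongest reply is that the two descriptions can coexist. A list could serve the first participants, or break ties, with minimisation taking over afterwards; or the authors may have used the term minimisation loosely for a list stratified by the two factors. That is fair. A reader might infer that the two methods can never be combined, and the document does not support that. What stands is narrower: the article describes neither hybrid, and the stratified-list reading fails on its own block sizes.

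It may also be said that a journal article leaves such details to the full protocol. That would answer an omission. Here the generator, block sizes, factors and cut-point are all stated, and the statements do not fit together. The figures are not available to this review, so it cannot be excluded that one of them helps; no text section does.

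Two stronger readings are tempting and should not be drawn.

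- **Predictable allocation.** The Blinding section concedes that "The lack of inhalation in the control group cannot be masked", and no random element is given for the minimisation. But such an element is a detail an article may omit, an unmasked control arm would be visible under any method, and nothing shows that staff could choose the order of enrolment.
- **A calculable shift in the result.** A split of 2 against 6 medication users between arms of 13 is (6 − 2)/13 = 31 percentage points. With a fall 10 points larger in users, the arm difference would move by about 3 points; with 5 points, by about 1.5. The document gives neither the number of users nor their fall, and the calculation supposes that allocation ignored a factor the protocol says it used.

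Finally, the adjusted analysis could sit in a separate analysis plan. That is possible, but the article names a one-way ANOVA, which by definition has no covariates.

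**Conclusion.** The point holds as an inconsistency in what the protocol states. The method that determines a participant's arm cannot be identified. Under the stratified-block reading, all three stated block sizes fail to divide by the number of arms. One factor has a gap at exactly 5 years, which is minor and is closed by one symbol.

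The block-size fault concerns balance within blocks. It does not show that the final arms will be unequal, since unequal blocks can offset one another across the list. Nor does it show that allocation was not random.

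These conclusions rest on the text alone. Only the 45% disagreement figure depends on assumptions, and the conclusion does not need it. No effect on the FEV1 comparison can be quantified from the document.

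**What to change.** 1. State which method has actually been used. The Trial status section schedules the first two of three test dates for December 2012 and February 2013, both before publication in July 2013. The first step is therefore to document what was done. Switching to a different method for the last date would put two methods into one small trial.
2. If the method is a stratified list, say so, remove the reference to minimisation, and use block sizes that are multiples of three (for example 3 and 6) for the remaining allocations. If it is minimisation, delete the blocks. If it is a hybrid, say which participants each rule governs.
3. Define the training levels as <5 and >=5 years, and record how any skater with exactly 5 years has been classified so far.
4. Replace the unadjusted one-way ANOVA for the percentage fall in FEV1 with a linear model (ANCOVA) containing arm, training-years level and current asthma medication, with Tukey-adjusted pairwise comparisons.

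The cost is a rewritten paragraph, a corrected list if blocks are in use, two residual degrees of freedom and slightly more analysis work. The model should be fixed before outcomes are compared by arm.
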